### Outcomes

The primary outcome for this study is 28-day mortality rate among preterm infants. For this primary analysis, the denominator will include:All live births weighing greater than 1000 g and less than 2500 gAll live births weighing between 2501 g and 3000 g with a documented GA of less than 37 weeksAll fresh stillbirths weighing greater than 1000 g and less than 2500 gAll fresh stillbirths weighing between 2501 g and 3000 g with a documented GA of less than 37 weeks

This outcome will be measured by comparing mortality rates of preterm infants at 28 days after delivery across the intervention and control arms to determine the effect of the package of facility-level interventions. The upper limit of 3000 g (which is coupled to a documented GA of less than 37 weeks) was agreed upon based on INTERGROWTH-21st standards. At this weight, we assume that we will capture 90% and 97% of < 34-week infants and 60% and 70% of < 37-week infants, for female and male children, respectively [22]. The lower limit of inclusion for the primary analysis was set at 1000 g to align with the *International Classification of Diseases 10th revision* (ICD 10) definition of late fetal death (i.e., birthweight of > 1000 g or > 28 weeks’ gestation) [6]. However, data on infants with signs of life born weighing < 1000 g will be followed for secondary data analyses, including outcomes at 28 days of life. Selected secondary outcomes are listed in Table 2.We include additional information as to how they will be measured and how often during the study duration.

**Table 2 Tab2:** Select secondary outcomes

Secondary outcome	How variable will be measured	Time frame
Data quality of key indicators in facility-based registers (includes GA, facility discharge status, preterm birth incidence)	GA-birthweight concurrence, DQAs and mSCC data review or QI indicators	Baseline through study completion, an average of 18 months; at least quarterly
Pre-discharge mortality among all infants > 1000 g	Clinical record review at facility	Baseline and through study completion, an average of 18 months
Facility-based maternal mortality	Clinical record review at facility	Baseline and through study completion, an average of 18 months
Perinatal mortality (fresh stillbirths and deaths within 7 days) among eligible preterm infants (includes pre-discharge mortality)	Parental report at 28 days and clinical record review at facility	Baseline and through study completion, an average of 18 months

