### Sample size and power calculations

Our primary analysis will combine data across our selected facilities in Kenya and Uganda. Since we will exclude the referral hospitals from our primary analysis, the project takes place in 20 facilities with an expected volume of 46,000 deliveries over 24 months. In an initial calculation, prior to baseline data collection, we assumed an average preterm birth rate of 12% and expected to see about 5500 preterm deliveries within this period. We assumed a 25% loss-to-follow-up rate for eligible cases. This yields at least 200 projected preterm deliveries per facility with known 28-day mortality outcome.

Detectable effect sizes were estimated by standard *t* test procedures adjusted to account for the design effect due to clustering of outcomes within facilities to attain 80% power while maintaining type I error at 5%. At a 25% 2-year cumulative incidence of 28-day mortality across both countries in the absence of the intervention, this would allow us to detect a 25% reduction in cumulative incidence if the between-cluster outcome coefficient of variation is 0.2 or below. If this coefficient increases to 0.3, we would be powered to detect a 30% reduction. If it increases to 0.4, we would be powered to detect a 40% reduction.

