### Challenges and opportunities

Several challenges will need to be overcome in order to ensure the success of this study. First, GA accuracy remains to be a major obstacle in these settings. Lack of early ultrasound, coupled with late antenatal care-seeking practices and inherent challenges with using LMP, makes GA difficult to robustly capture. Second, using routine data sources may uncover challenges with data quality and completeness. While data strengthening is a foundational intervention across all of our sites, staff turnover, industrial strikes, burnout, and other contextual factors may impact data. Third, although this is a package of interventions, each of the component parts has its unique strengths and challenges. Uptake and acceptability of the individual components may vary. Lastly, our trial focuses on improving facility-based care during the intrapartum and immediate newborn period; however, our primary outcome is 28-day mortality among preterm infants (denominator defined as the sum of live born infants weighing greater than 1000 g and less than 2500 g or GA of less than 37 weeks and weight less than 3000 g plus fresh stillbirths with the same weight and GA criteria). The ability to monitor post-discharge health or activities will not be possible within the scope of this project.

Several research opportunities arise within this trial. First, as preterm birth is often described as a syndrome [24], this study will allow for nested studies examining maternal, fetal, and placental risk factors that contribute to preterm birth. As such, preterm birth phenotyping studies using the framework described by Barros et al. (2012) will be nested at some of our sites [25]. Second, as GA assessment will prove to be a challenge in many of our sites, this poses a unique opportunity to test other measures to more accurately estimate GA. This may include, for example, studies focused on discovery of biomarkers and/or comparison of various anthropometric measures.

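### The trial is sized on all preterm births with a 25% control mortality, but the primary denominator is defined by birthweight, so neither figure describes the analysed infants; exactly 2500 g also falls between its two weight bands

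*Protocol article*

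**What the plan says.** Sample size and power calculations assumes "20 facilities with an expected volume of 46,000 deliveries over 24 months". On the number of cases it says that "we assumed an average preterm birth rate of 12% and expected to see about 5500 preterm deliveries within this period". The status it gives to this count is "In an initial calculation, prior to baseline data collection". Then "We assumed a 25% loss-to-follow-up rate for eligible cases", and the stated result is: "This yields at least 200 projected preterm deliveries per facility with known 28-day mortality outcome". The detectable reductions that follow (25%, 30% and 40% at coefficients of variation 0.2, 0.3 and 0.4) assume 25% mortality at 28 days without the intervention.

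Outcomes defines who is analysed, for live births and fresh stillbirths alike. One band is above 1000 g and below 2500 g, with no gestational-age condition. The other is 2501 g to 3000 g with documented gestational age under 37 weeks. The same section assumes that the 3000 g limit captures 60% and 70% of under-37-week "infants, for female and male children, respectively".

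The Abstract uses the same two bands. Study population uses the same split at 2500/2501 g to decide which mothers are asked to consent to 28-day follow-up, and says these parameters were chosen from baseline data. Challenges and opportunities restates the primary denominator as above 1000 g and below 2500 g, or "GA of less than 37 weeks and weight less than 3000 g plus fresh stillbirths with the same weight and GA criteria".

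**The concern.** The sizing counts one population and the primary analysis uses another. Two differences run in opposite directions:

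- About a third of preterm infants are expected to weigh too much to enter. The sizing does not remove them.
- Term infants under 2500 g do enter. The sizing does not count them.

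The number of analysable infants per facility is then unknown, and so is whether 25% is a sensible control mortality for the mixture. The printed detectable reductions rest on both.

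The boundary is a separate problem. As written in the Abstract, Study population and Outcomes, an infant recorded at exactly 2500 g belongs to neither band. The Discussion's wording admits that infant if gestational age is under 37 weeks. The primary denominator is thus stated in two ways. Because Study population selects for follow-up with the same split, a 2500 g infant discharged alive would not be followed, and the 28-day outcome could not be recovered at analysis.

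**Working it through.** **1. The plan's own figure.** Inputs from Sample size and power calculations: 46,000 deliveries, 12% preterm, 25% loss, 20 facilities.

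- 46,000 × 0.12 = 5520 (printed as about 5500)
- 5520 × 0.75 / 20 = 207 per facility (printed as at least 200)

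The figure reproduces with no other reduction, so every preterm birth was counted.

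**2. Preterm infants inside the denominator.** Apply the 60% and 70% capture from Outcomes as a simple multiplier:

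- 60%: 5520 × 0.60 = 3312; × 0.75 / 20 = 124 per facility
- 70%: 5520 × 0.70 = 3864; × 0.75 / 20 = 145 per facility

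This is a floor for the denominator, because infants under 2500 g who are not preterm are added to it.

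**3. Term infants needed to reach 200.** Eligible infants required before loss: 200 × 20 / 0.75 = 5333.

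- At 70% capture: 5333 − 3864 = 1469, or 1469 / 46,000 = 3.2% of births
- At 60% capture: 5333 − 3312 = 2021, or 2021 / 46,000 = 4.4% of births

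The article gives no rate for term infants under 2500 g, so it cannot be said which side of this range applies.

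**4. How much the count could matter.** The article does not give its variance formula. I used an unmatched comparison with 10 facilities per arm, p0 = 0.25, p1 = p0(1 − reduction), m infants per facility, coefficient of variation k, and

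variance = [p0(1−p0)/m + p1(1−p1)/m + k²(p0² + p1²)] / 10,

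with power from a two-sided 5% t test on 18 degrees of freedom. For k = 0.2 and a 25% reduction (p1 = 0.1875):

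- m = 207: (0.000906 + 0.000736 + 0.003906)/10 = 0.000555; 0.0625/√0.000555 = 2.65; power 71%
- m = 145: power 66%
- m = 124: (0.001512 + 0.001229 + 0.003906)/10 = 0.000665; 0.0625/√0.000665 = 2.42; power 63%

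In this model the smaller count costs about 5-8 points at k = 0.2. At k = 0.3 and 0.4, with the 30% and 40% reductions, it costs about 2-4 points, because variation between facilities dominates. With the same variance and a normal approximation, the reduction detectable at 80% power and k = 0.2 moves from 26.3% (m = 207) to 27.7-28.5%. The rows for 145 and 124 hold only if no term infant enters.

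**5. How much the mortality could matter.** Hold m = 207, k = 0.2 and a 25% reduction, and vary control mortality. The lower values are assumptions, not figures from the article.

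- 25%: power 71%
- 20%: power 67%
- 15%: power 61%

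A count made up with lower-risk infants could cost as much as the shortfall it repairs.

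**6. The boundary at 2500 g.** The bands in the Abstract, Study population and Outcomes stop below 2500 g and resume at 2501 g, so a recorded weight of 2500 g satisfies neither. Under the second limb in Challenges and opportunities, 2500 g with gestational age under 37 weeks does satisfy the rule. The definitions disagree for that infant.

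**The case against.** The printed arithmetic is correct on its inputs, and the section labels it as done "In an initial calculation, prior to baseline data collection". Study population says the weight rule was chosen from baseline data, so the sizing appears to predate the rule. This stands as an explanation. It does not remove the problem: the article prints detectable reductions from the old inputs only and reports no update, although baseline data existed.

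A reader might infer that the trial has only 124-145 analysable infants per facility, or that its power is 63-66%. The document does not support that. Outcomes admits infants under 2500 g at any gestational age, so those figures hold as totals only if that group is empty of term infants. In addition, the 71% starting point comes from my model and not from the article's 80%. That gap has nothing to do with capture.

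A reader might also suppose that many infants are lost at exactly 2500 g because recorded weights tend to be rounded. The article gives no weight distribution, so the number cannot be stated, and no effect on power is shown. It is also fair to say that the source of the 25% mortality is not given. That it was set for preterm infants is the natural reading of a sizing built on preterm deliveries, but it is not stated outright.

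**Conclusion.** The point holds as a mismatch of populations, not as a demonstrated shortfall. The yield of 207 per facility counts all preterm births. On the protocol's own capture assumption the primary denominator holds 124-145 preterm infants per facility with known outcome, plus an unstated number of term infants under 2500 g. The total reaches 200 only if those term infants are about 3.2-4.4% of births. The net count may be below, at or above 200, and the direction of any change in power is open.

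This rests on capture acting as a simple multiplier, on 25% loss applying to all eligible cases, and on 46,000 deliveries as printed. That last figure needs checking in its own right: Setting and site selection gives 9000 + 7500 deliveries a year at matched sites, or 33,000 over 24 months.

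The boundary defect needs no assumption: 2500 g is excluded in three places and, with gestational age under 37 weeks, included in a fourth. Its size cannot be determined from the article.

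**What to change.** 1. Make the weight bands contiguous in the Abstract, Study population and Outcomes, for example 2500 g and below, then above 2500 g up to 3000 g with documented gestational age under 37 weeks, or an equivalent split. Make Challenges and opportunities match, including whether 3000 g itself is in.

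2. In Sample size and power calculations, replace the 12% rate with the proportion of births that meet the Outcomes definition, and the 25% with the 28-day mortality of those same infants. Take both from the baseline registers. Then restate the cases per facility and the detectable reductions.

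3. Do not simply multiply by 60-70%. That would size the trial on captured preterm infants alone and leave out the term infants under 2500 g whom Outcomes includes.

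The cost is wording changes and one recalculation from data in hand. The downside is that the printed cases per facility and detectable reductions may become less favourable.

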## Methods

### Trial design

This study is a pair-matched, cluster randomized controlled trial (CRCT) among 20 public sector health facilities in the Busoga Region of Uganda (four facilities) and in Migori County, Kenya (16 facilities, including 14 public facilities and two not-for-profit missionary hospitals). The full intervention package (data strengthening (DS), modified Safe Childbirth Checklist (mSCC), PRONTO provider training, and quality improvement (QI)) will be introduced to 10 facilities (intervention arm); the remaining 10 facilities will receive DS + mSCC (control arm) (Fig. 1). All facilities will begin with DS + mSCC intervention components in order to capture preliminary data for baseline and facility matching, as well as to standardize definitions of key indicators related to GA and newborn outcomes. Roll-out of mSCC and support will differ between the control and intervention sites, in that the latter will receive additional mSCC mentorship and support through synergies with PRONTO and QI. The intervention package will be delivered at the facility level, while outcomes will be measured at both an individual and facility level.

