### Setting and site selection

The study regions of Migori County, Kenya and Busoga Region, Uganda were selected based on in-country stakeholder input. Prematurity burden and presence of synergistic parallel maternal/newborn research or implementation studies were considered. Health facilities were asked to participate in this study by in-country partners. Formal approval from facility leadership was obtained before any activities commenced. Given that facilities were not selected from a target population of hospitals, the intervention effects should be interpreted as impact evaluation of the intervention package implemented at the said facilities. A complete list of all facilities can be found at the clinical trial registration (ClinicalTrials.gov, ID: NCT03112018).

The Busoga Region of Eastern Uganda contains approximately three million people, or 10% of Uganda’s population, with over 80% of residents living on less than US$1 per day [21]. The estimated preterm birth rate for Uganda is 13.57% and the neonatal mortality rate is 21 per 1000 live births [3, 4]. Our selected six health facilities include approximately 22,000 deliveries per year, with 9000 deliveries from the four hospitals pair-matched in this study. Migori County, located in southwestern Kenya, has a population of approximately 917,170, wherein 43% of the population lives below the poverty line [21]. The estimated preterm birth rate for Kenya is 12.30% and the neonatal mortality rate is 23 per 1000 live births [3, 4]. Our 17 selected Migori County health facilities include approximately 10,000 deliveries per year, with 7500 deliveries at pair-matched sites.

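### The detectable reductions rest on one common facility size of about 200 outcomes, which the article's own delivery volumes contradict; allowing for the real sizes costs about 2–6 points of power with facilities weighted equally and about 18–21 with infants weighted equally

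*Protocol article*

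**What the plan says.** Under Trial design, the study has ten matched pairs, "in the Busoga Region of Uganda (four facilities) and in Migori County, Kenya (16 facilities" in all). Setting and site selection gives yearly volumes by country: for Uganda, "with 9000 deliveries from the four hospitals pair-matched in this study", and for Kenya, "with 7500 deliveries at pair-matched sites".

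Sample size and power calculations works from a single total: "the project takes place in 20 facilities with an expected volume of 46,000 deliveries over 24 months". It then says that "we assumed an average preterm birth rate of 12% and expected to see about 5500 preterm deliveries within this period", takes off 25% for loss to follow-up, and concludes that every facility will have at least 200 preterm deliveries with a known 28-day outcome. Detectable effects come from a t test "adjusted to account for the design effect due to clustering of outcomes within facilities", with one between-cluster coefficient of variation (CV) at a time. Against 25% control mortality, the printed reductions at 80% power and 5% type I error are 25% (CV 0.2), 30% (CV 0.3) and 40% (CV 0.4). No allowance for unequal facility sizes is mentioned.

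On the primary contrast, Outcomes speaks of "comparing mortality rates of preterm infants at 28 days after delivery across the intervention and control arms". Analyses plans names hierarchical targeted maximum-likelihood estimation (TMLE) that uses the pair-matched assignment, with delivery volume and country among the facility covariates. Neither section says whether facilities or infants carry equal weight.

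**The concern.** A per-facility minimum of 200 is obtained by dividing a total by 20, so it is an average presented as a floor. The site volumes imply about 2250 deliveries a year at each Ugandan hospital and about 469 at each Kenyan facility. Sixteen of the 20 clusters would then fall, on average, well below the size on which power was computed.

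Unequal sizes matter in two ways. If facilities are weighted equally, the small Kenyan facilities add binomial noise. If infants are weighted equally, two Ugandan pairs carry more than half of the weight and between-facility variation is averaged over fewer effective pairs. Either way the printed reductions are too optimistic, and readers rely on them when they judge whether a null result is informative.

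**Working it through.** **Inputs.** From the sample size section: 46,000 deliveries, 12% preterm, 25% loss, control risk p0 = 0.25, CV k = 0.2, 0.3 or 0.4, alpha 5%, power 80%. From the site section: 9000 and 7500 deliveries a year. Assumptions of mine: two-sided test; t with 18 df; equal sizes within country; pairs formed within country (two Ugandan and eight Kenyan facilities per arm); no credit for matching or covariates.

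**The plan's own size.** 46,000 × 0.12 = 5520, printed as about 5500. Then 5500 × 0.75 = 4125, and 4125 / 20 = 206. The average reproduces.

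**Sizes implied by the site section.** The Ugandan share is 9000 / 16,500 = 54.5%.
- Ugandan hospital: 4125 × 0.545 / 4 ≈ 562.
- Kenyan facility: 4125 × 0.455 / 16 ≈ 117.
- With the site section's total (16,500 × 2 = 33,000 deliveries, so 33,000 × 0.12 × 0.75 = 2970 outcomes): about 405 and 84.
- Size CV: yearly volumes 2250 (×4) and 468.75 (×16) have mean 825 and SD 712.5, so CV = 0.86. For these country totals this is a floor, because it ignores variation within country.

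**Variance of the arm difference**, with weights w_j summing to 1 over the ten facilities of an arm and m_j outcomes in facility j:

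V = Σ w_j² [ p0(1−p0)/m_j + p1(1−p1)/m_j + k²(p0² + p1²) ]

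Power comes from the non-central t with non-centrality (p0 − p1)/√V.

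**Worked case, k = 0.2, 25% reduction (p1 = 0.1875).** The binomial numerator is 0.1875 + 0.1523 = 0.3398. The between-facility term is 0.04 × (0.0625 + 0.0352) = 0.00391.
- Equal sizes: V = (0.3398/206.25 + 0.00391)/10 = 0.000555; non-centrality 0.0625/0.0236 = 2.65; power 71%.
- Site volumes, equal facility weights: bracket 0.00451 (Uganda) and 0.00681 (Kenya); V = (2 × 0.00451 + 8 × 0.00681)/100 = 0.000635; non-centrality 2.48; power 65%.
- Site volumes, infant weights: w = 562.5/2062.5 = 0.273 (Uganda) and 117.2/2062.5 = 0.0568 (Kenya); V = 2 × 0.273² × 0.00451 + 8 × 0.0568² × 0.00681 = 0.000847; non-centrality 2.15; power 53%. Effective pairs by weights alone: 1/Σw² = 5.7.

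**All three scenarios, 4125 outcomes**

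| | k = 0.2, 25% | k = 0.3, 30% | k = 0.4, 40% |
|---|---|---|---|
| Power, equal sizes | 71% | 61% | 68% |
| Power, site volumes, facility weights | 65% | 58% | 66% |
| Power, site volumes, infant weights | 53% | 42% | 47% |
| Detectable at 80%, equal sizes | 28% | 36% | 45% |
| Detectable at 80%, facility weights | 29% | 38% | 46% |
| Detectable at 80%, infant weights | 33% | 45% | 56% |

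The loss due to unequal sizes alone is 2–6 points with facility weights and 18–21 with infant weights. With 2970 outcomes it is 3–7 and 16–20 points.

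**Sensitivity to the conflicting totals.** The two sections differ by 46,000 − 33,000 = 13,000 deliveries. Keeping 4125 outcomes:
- Extra births all Kenyan: Ugandan share 18,000/46,000 = 39%, effective pairs 8.1, infant-weighted loss 6–8 points. The average Kenyan facility still has only about 157 outcomes.
- Extra births all Ugandan: share 31,000/46,000 = 67%, effective pairs 4.2, infant-weighted loss 28–32 points.

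**The case against.** The strongest objection concerns weighting. A reader might infer from the Outcomes wording, and from the statement that data are combined across facilities, that infants are weighted equally and that the trial therefore has the precision of about six pairs. The article does not establish that. Combining data can simply mean analysing the two countries together. A t test with a between-cluster CV fits a comparison of facility rates. The TMLE description gives no weights, and an article may leave that detail to the full protocol or analysis plan. This objection stands: the 18–21 point loss is conditional, and the smaller figure applies if facilities count equally.

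It is also fair that most of the shortfall from 80% under facility weights is there before unequal sizes enter. Under my assumptions the equal-size calculation gives only 61–71%, and even a two-sided normal approximation needs reductions of 26, 35 and 43%. That gap is a separate matter and should not be attributed to facility size.

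Matching on delivery volume and adjustment for facility covariates may recover some precision, and my figures give no credit for either. The sample size section also labels its inputs as preceding baseline data. Neither point reconciles a floor of 200 with volumes printed in the same article.

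A reader might further infer that the primary test would over-reject. The documents do not support that: no infant-weighted pair t test is planned, and the TMLE variance is not described in enough detail to attach an error rate. Nor do they support a demand that the facility-level effect be primary. Both effects are legitimate targets.

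**Conclusion.** The point holds as an internal contradiction with a conditional cost. At least 200 known outcomes per facility is wrong for the average Kenyan facility under every reading of the delivery totals tried here (84, 117 or 157). At the printed reductions, power is below 80% under either weighting when the site volumes are used. How much of that is due to unequal sizes depends on two things the article leaves open: the weighting of the primary effect, and which delivery total is right. With facility weights the cost is small; with infant weights it is material. The figures assume a two-sided test, t with 18 df, pairing within country, equal sizes within country, and no gain from matching or covariates.

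**What to change.** In Sample size and power calculations:
- Replace the floor of 200 per facility with the expected sizes by country, or by facility if known.
- Reconcile 46,000 deliveries over 24 months with the 33,000 implied by Setting and site selection.
- Reprint the detectable reductions from those volumes for the weighting that the primary TMLE will use. On present figures these are about 29, 38 and 46% with facility weights, or 33, 45 and 56% with infant weights. With 33,000 deliveries they become about 31, 39 and 47%, or 34, 46 and 56%.

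In Analyses plans, add one sentence naming that weighting, fixed before the unblinded comparison. If the full protocol or analysis plan already states it, repeat it here.

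The cost is one recalculation and a few sentences, with no new data. The downside is that the printed detectable reductions become less favourable.

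### The stated detectable reductions (25%, 30%, 40% at CV 0.2, 0.3, 0.4) do not have 80% power under a two-sided, unmatched t test with 10 facilities per arm: power is about 70%, 61% and 68%

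*Protocol article*

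**What the plan says.** The article describes a pair-matched cluster trial in which the full package "will be introduced to 10 facilities (intervention arm); the remaining 10 facilities will receive DS + mSCC (control arm"). The section on sample size and power gives these inputs:

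- Cluster size: "This yields at least 200 projected preterm deliveries per facility with known 28-day mortality outcome".
- Attrition, already taken off that figure: "We assumed a 25% loss-to-follow-up rate for eligible cases".
- Control risk: "At a 25% 2-year cumulative incidence of 28-day mortality across both countries in the absence of the intervention".
- Error rates: "to attain 80% power while maintaining type I error at 5" per cent. Sidedness is not given.
- Method: ordinary t test procedures with a design effect for clustering by facility.

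Three claims follow. The first, for the smallest CV, is that "this would allow us to detect a 25% reduction in cumulative incidence if the between-cluster outcome coefficient of variation is 0.2 or below". The second pairs a CV of 0.3 with a 30% reduction. The third, for the largest CV considered, reads "If it increases to 0.4, we would be powered to detect a 40% reduction". The section mentions no within-pair correlation and no gain from covariate adjustment. The analysis section does plan a targeted maximum-likelihood estimator that uses the pairing and baseline covariates.

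**The concern.** With only 10 facilities per arm, between-facility variation dominates the standard error once the CV reaches 0.2 or more. The three claimed reductions look too small for that many clusters.

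These sentences are the article's only statement of what the trial can detect. If they are too optimistic, a null result will be read as stronger evidence against a 25% to 40% reduction than the design supports. The stated risk of missing each effect is 20%. Under the test described, read as two-sided, it is about 30%, 39% and 32%.

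**Working it through.** **Cluster size.** 46,000 deliveries × 0.12 = 5520, which the article rounds to 5500. Then 5500 × 0.75 / 20 = 206 per facility, so the article's figure of at least 200 is reproduced. I use m = 200.

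**Inputs.** c = 10 facilities per arm; m = 200; p0 = 0.25; p1 = 0.25 × (1 − reduction); k = CV of the true facility rates in each arm. Assumptions: two-sided 5%, no matching gain.

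**Formulas.**
- V = p0(1−p0)/m + p1(1−p1)/m + k²(p0² + p1²)
- Noncentrality = (p0 − p1) / √(V/10)
- Power from the noncentral t distribution with 18 df (two-sided critical value 2.101)

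| k | Reduction | p1 | Sampling part of V | Between-facility part | V | Noncentrality | Power, t 18 df | Power, normal |
|---|---|---|---|---|---|---|---|---|
| 0.2 | 25% | 0.1875 | 0.00170 | 0.00391 | 0.00561 | 0.0625/0.02368 = 2.640 | 70.4% | 75.2% |
| 0.3 | 30% | 0.175 | 0.00166 | 0.00838 | 0.01004 | 0.0750/0.03169 = 2.367 | 61.0% | 65.8% |
| 0.4 | 40% | 0.15 | 0.00158 | 0.01360 | 0.01518 | 0.1000/0.03896 = 2.567 | 68.0% | 72.8% |

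A beta-binomial simulation of the same t test (40,000 runs) gave 70.8%, 60.9% and 69.2%.

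**Solving for other quantities at 80% power (two-sided, 18 df).**
- Detectable reductions: 27.7%, 36.5% and 45.2%.
- Largest CV at which 25%, 30% and 40% hold: about 0.17, 0.23 and 0.34.
- Facilities per arm needed for the stated reductions: 13, 16 and 13.

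**Variants.** Power for the three stated combinations, in order of CV:

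| Variant | 0.2 | 0.3 | 0.4 |
|---|---|---|---|
| m = 275 (no loss to follow-up), two-sided t | 74.1% | 63.0% | 69.3% |
| Log-ratio scale, two-sided t | 71.2% | 62.7% | 71.7% |
| One-sided 5%, t 18 df | 81.4% | 73.6% | 79.5% |
| One-sided 5%, normal | 84.0% | 76.5% | 82.2% |
| Paired t, 9 df, no matching gain | 65.3% | 56.0% | 62.9% |
| Paired t, 9 df, within-pair correlation 0.5 | 82.1% | 77.1% | 83.5% |

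The last row subtracts 2ρk²p0p1 from V, with ρ = 0.5 chosen for illustration. On this basis the paired test overtakes the unpaired one once ρ exceeds about 0.14 to 0.17. It reaches 80% at ρ of about 0.45, 0.56 and 0.43.

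**The case against.** The best defence is that the test was one-sided and the results were rounded. At one-sided 5% with 18 df, the detectable reductions are 24.5%, 32.4% and 40.2%, which to the nearest 5 points are 25%, 30% and 40%. That may be how the figures arose. But the article states neither a one-sided alpha nor such rounding, and power at CV 0.3 for a 30% reduction remains 73.6%. What stands is that sidedness has to be stated before the figures can be judged finally.

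The second defence is matching. Facilities are paired on factors chosen for their relation to the outcome, and the analysis uses the pairs and covariates. With a within-pair correlation of 0.5, the detectable reductions would be about 24.4%, 31.0% and 38.3%. This is possible, but the power section assumes no such correlation and attributes its figures to a t test with a design effect.

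Three stronger readings are tempting and are not supported:

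- A reader might infer that analysing the pairs necessarily lowers power. It does so only if the stated CV is a within-pair CV or the matching gains little.
- A reader might infer that no enrolment could rescue the CV 0.3 and 0.4 claims. With unlimited infants per facility, the two-sided unmatched t test does stop at about 69% and 73%, but a one-sided test reaches 80.1% and 83.2%.
- A reader might infer that the planned analysis itself is underpowered by this amount. That is not shown, because its gain in precision is not quantified.

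The article calls the birth-rate and volume assumptions an initial, pre-baseline calculation. It gives no later power figures, so the three claims stand as published.

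**Conclusion.** The point holds for the test the article describes. Read as a two-sided 5%, unmatched t test, the three claims fall short of 80% power by about 10, 19 and 12 percentage points. The reductions that do have 80% power are about 3, 7 and 5 points larger than stated. The normal approximation, the log scale and removal of all attrition leave the shortfall in place. The one-sided reading comes close at CV 0.2 and 0.4 but not at 0.3.

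The result rests on two-sidedness, the same CV in both arms, equal facility sizes of 200 and no gain from matching or covariates. The direction and size of any pairing effect remain open.

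**What to change.** Rewrite the power paragraph as follows:

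1. State whether the 5% is one-sided or two-sided.
2. For a two-sided, unmatched t test, give the detectable reductions as about 28%, 37% and 45% at CV 0.2, 0.3 and 0.4. Alternatively, keep 25%, 30% and 40% and give the largest CVs at which they hold (about 0.17, 0.23 and 0.34).
3. Say whether the CV is within-pair or across all facilities.
4. If a gain from matching or covariate adjustment is relied on, state its assumed size and show the paired figures (9 df) under it. Set beside them the no-gain case of about 29%, 39% and 48%.

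This costs one paragraph and no extra patients or facilities. The drawback is a less favourable stated power.
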